### Participants

Patients admitted to the AGCH are eligible for inclusion in the study. However, patients are excluded from the study if: (1) the attending physician judges that the patient is too ill to participate, for example, the patient is terminally ill, (2) the patient or legal representative does not consent to participate, or (3) the patient or legal representative does not speak or understand Dutch or English. In the case of cognitively impaired or delirious patients, patients can only be included if a legal representative consents to participation and acts as healthcare proxy. Cognitive functioning is assessed by the attending physician and confirmed by the researcher by conducting a Mini-Mental State Examination (MMSE).^31^ An MMSE score of 15 or less indicates severe cognitive impairment, in which the approval of a legal representative will be sought.

### Historical control groups

We selected two completed cohort studies that were conducted by our research group as historical control groups. We expect that the patients from these cohorts have similar admission diagnoses as those who can be admitted to the AGCH, namely, diagnoses that are ambulatory care sensitive conditions such as infections and exacerbations of chronic obstructive pulmonary disease (COPD) or heart failure.^32^ Patients in these two cohorts were admitted to internal medicine, cardiology, pulmonology and geriatrics departments. These departments admit patients with diagnoses similar to those that can be admitted to the AGCH. In addition, we have selected these cohorts as control groups as the patients come from the same area as the studied population admitted to the AGCH, that is, the greater Amsterdam area. The first control group from the Transitional Care Bridge Study consists of 674 patients who were recruited between September 2010 and March 2014.^33^ Participants were patients of 65 years and older hospitalised for at least 48 hours. Proxy consent was provided for participants suffering from severe cognitive impairment (MMSE ≤15). They participated in a negative randomised controlled trial that assessed the effectiveness of a nurse-led transitional care programme in preventing functional decline.^33^ The second control group from Hospital-Associated Disability and impact on daily Life study (Hospital-ADL study) consists of 401 patients who were recruited between October 2015 and June 2017.^10^ These participants were enrolled in a prospective cohort studying the trajectory of functional decline in older hospitalised adults. Participants were aged 70 years and older and were hospitalised for at least 48 hours. Patients suffering from severe cognitive impairment (MMSE ≤15) and delirium were excluded from participation. For the detailed methodology and inclusion criteria of the two control cohorts, please refer to the study protocols and papers of these studies.^10 33–35^

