## Methods

### Setting

The AGCH opened in July 2018. It serves the south-eastern part of Amsterdam and its surrounding areas (an area with approximately 147 500 inhabitants).^28^ The AGCH is a 23-bed facility within a skilled nursing facility. The hospital has 24 hours geriatric and nursing assistance. Physiotherapy and routine laboratory testing are available during the workweek and simple X-ray is available once a week. The population that is eligible for admission to the AGCH are patients with a combination of an acute medical problem requiring hospitalisation (eg, pneumonia, exacerbation of heart failure or a urinary tract infection) and a geriatric condition (eg, delirium, cognitive impairment, falls, or functional impairment). Additionally, patients have to be haemodynamically stable and should not require complex diagnostic testing. In general, patients will not be admitted if they have the following exclusion criteria: (1) require care that can only be provided at an intensive care unit, (2) require surgery, (3) require urgent treatments or diagnostic tests that can only be provided in-hospital (eg, endoscopy, interventional radiology), (4) do not need hospital care but require transfer to a skilled nursing facility and (5) live in another region of the Netherlands.

Patients are directly admitted to the AGCH from the ED of the Amsterdam UMC-location Academic Medical Centre (AMC) in Amsterdam, which is a 1000-bed academic hospital with approximately 30 000 ED visits yearly. After the on-call geriatrician has assessed whether the patient is eligible for AGCH admission and the patient or representative has agreed to admission, the patient is transferred to the AGCH by ambulance. Since October 2019, patients can also be transferred from the EDs of other hospitals in Amsterdam. In the future, we plan to admit patients from home or general practice offices. Patients are admitted between 8.00 am and 23.00 pm, 7 days a week. At admission, a Comprehensive Geriatric Assessment (CGA) is conducted.^29^ The CGA gives an overview of all medical, functional, psychological and social problems. The CGA is discussed during multidisciplinary team meetings and used to formulate a care plan for each patient. For an overview of the admission process, the admission criteria and the components of this intervention, see figure 1.

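### The AGCH admission gate on stability and hospital-only care has no stated counterpart for the historical controls, and the listed covariates can adjust for it only in part

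*Protocol article*

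**What the plan says.** **AGCH entry (Setting).** Each patient needs an acute problem plus a geriatric condition. Beyond that, "patients have to be haemodynamically stable and should not require complex diagnostic testing". The list of reasons for refusal opens softly: "In general, patients will not be admitted if they have the following exclusion criteria". It covers intensive-care needs and surgery, and patients who "require urgent treatments or diagnostic tests that can only be provided in-hospital (eg, endoscopy, interventional radiology"). The gate is applied to each patient at the emergency department; transfer follows only "After the on-call geriatrician has assessed whether the patient is eligible for AGCH admission" and the patient or representative has agreed.

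**Control selection (Historical control groups).** Two completed cohorts are used, of 674 and 401 patients. They are described by minimum age (65 or 70 years), a stay of at least 48 hours, handling of severe cognitive impairment (and delirium in the second cohort), region and department: "Patients in these two cohorts were admitted to internal medicine, cardiology, pulmonology and geriatrics departments". Comparability on clinical grounds is an expectation: "We expect that the patients from these cohorts have similar admission diagnoses as those who can be admitted to the AGCH". Detailed inclusion criteria are left to the cohorts' own protocols and papers.

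**Adjustment (Planned statistical analyses).** Inverse propensity weights target the average treatment effect, using covariates that differ at baseline or relate to readmission. Balance and overlap are to be checked. The Abstract speaks of matching instead.

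**The concern.** The intervention group is screened on acuity and the control group, as described here, is not. Diagnosis and department do not stand in for that screen: pneumonia or heart failure can present stable or unstable, and a medical or cardiology ward also takes patients who need the in-hospital procedures for which the AGCH refuses patients.

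If some controls would have been refused by the AGCH and their readmission risk differs from that of the rest, the 90-day readmission contrast includes that difference in case mix. The planned weights act only on measured covariates, and an overlap check cannot show non-overlap on something unmeasured. Targeting the average treatment effect adds a positivity problem, because the estimate then covers people for whom AGCH admission was not possible.

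**Working it through.** **1. The criteria side by side**

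| AGCH gate (Setting) | Stated for controls | Measured at baseline (Table 1 and Data collection) |
|---|---|---|
| Geriatric condition present | Not required | Largely: MMSE, delirium instruments, Katz-ADL, fall history, ISAR-HP |
| No surgery needed | Largely covered by non-surgical departments | Admission diagnosis only |
| No intensive care needed | Not stated; perhaps partly covered by department | No direct measure |
| Haemodynamically stable | Not stated | No vital signs or acute severity score |
| No complex diagnostics or urgent hospital-only care | Not stated | Only diagnostics performed during the AGCH stay, so after the gate |

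The last two rows, and part of the intensive-care row, are what mainly remain.

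**2. The plan's own figure (Sample size calculation)**

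Inputs: 34% (Hospital-ADL cohort) against 26% (assumed for the AGCH), two-sided alpha 0.05, power 80%, equal groups.

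n = [1.96·√(2·0.30·0.70) + 0.842·√(0.34·0.66 + 0.26·0.74)]² / 0.08² = 514 per group; the plan says 515. At 515 per group power is 80.1%. The figure reproduces, and this point does not depend on it. It supplies the yardstick of 8 points.

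**3. Possible size, additive form (assumed inputs)**

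Let s be the share of controls whom the AGCH would have refused and d their excess 90-day readmission risk. The documents give neither. With no true effect and no correction by weighting, bias = s × d:

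- 0.20 × 0.05 = 1.0 point; 0.40 × 0.05 = 2.0 points
- 0.20 × 0.10 = 2.0 points; 0.40 × 0.10 = 4.0 points

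That is 1–4 points, or one eighth to one half of 8. Holding the overall control rate at 34%, these inputs imply risk ratios of about 1.15 (0.38/0.33) to 1.33 (0.40/0.30).

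**4. Possible size, wider ratio form (assumed inputs)**

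Let RR be the risk ratio of refusable against eligible controls. Eligible rate = 0.34 / (1 − s + s·RR); bias = 0.34 minus that rate.

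| s | RR | Eligible rate | Bias (points) | Chance of a significant false benefit, 515 v 515 |
|---|---|---|---|---|
| 10% | 1.25 | 33.2% | 0.8 | 5% |
| 20% | 1.5 | 30.9% | 3.1 | 18% |
| 30% | 1.5 | 29.6% | 4.4 | 33% |
| 30% | 2.0 | 26.2% | 7.8 | 78% |
| 50% | 2.0 | 22.7% | 11.3 | 98% |

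If refusable patients were readmitted less often (RR 0.67–0.8, s 10–50%), the sign reverses, by 0.7 to 6.7 points against the AGCH.

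**5. Cost of restricting the controls**

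Power = Φ{[0.08 − 1.96·√(p̄q̄(1/n₁ + 1/n₂))] / √(p₁q₁/n₁ + p₂q₂/n₂)}, with n₁ = 515 AGCH patients at 26%, n₂ controls at 34%, and p̄ the pooled rate. No allowance is made for weighting.

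| Controls | None removed | 20% removed | 30% removed | 50% removed |
|---|---|---|---|---|
| Both cohorts (1,075) | 90% | 88% (860) | 86% (752) | 81% (538) |
| 401-patient cohort only | 75% | 70% (321) | 66% (281) | 57% (200) |

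**The case against.** A reader might infer that patients the AGCH would have refused are certainly counted as usual care, and that the primary comparison is therefore biased in the AGCH's favour by design. The documents do not support that. The cohorts' detailed criteria are in papers not shown and may already exclude some of these patients. The AGCH exclusions hold only in general. No text says that all 1,075 controls must enter the primary analysis. Table 1 describes AGCH measurements only, and the supplementary table comparing the three cohorts is not shown. Admission diagnosis, comorbidity and frailty measures carry part of any acuity difference, and bias in either direction is possible. All of this stands, and it limits the point to a mismatch of unknown size and sign.

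It can also be said that trimming rules belong in an analysis plan and that the limitations already concede baseline differences. Trimming or matching, however, works on measured covariates. Who qualifies as a control is a protocol decision, and this article makes it. Strengths and limitations and the Discussion name baseline differences, non-randomisation and calendar time, but not the gate.

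Finally, a filter cannot act on acuity that was never recorded. That is correct, and the remedy must say so.

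**Conclusion.** The point holds in a limited form. The AGCH applies a patient-level gate, and the article states no counterpart for the controls. Surgery is largely dealt with by the choice of departments, and geriatric conditions are largely measurable and adjustable. Stability and need for hospital-only care are not measured directly by the listed covariates, so weighting can correct for them only partly, and average-treatment-effect weights reach beyond the patients who could have entered the AGCH.

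Neither the size nor the direction of the bias can be determined from the documents. The 1–4 point range rests on assumed shares of 20–40%, an assumed excess of 5–10 points and no help from weighting. The wider ratio assumptions give 0.8–11.3 points, or a reversal. Even the lower range is not negligible against a design difference of 8 points, so the control definition should be changed before the primary comparison is made.

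**What to change.** Under Historical control groups, add a rule along these lines:

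*For the primary comparison, controls are limited, as far as the cohort data record it, to patients who would have met the AGCH admission criteria: a qualifying acute diagnosis with at least one geriatric condition (cognitive impairment, falls, functional impairment, or delirium where recorded); haemodynamic stability; and no need at presentation for complex diagnostics, intensive care, surgery, or urgent tests or treatment available only in hospital. Eligibility is judged blind to outcome. The comparison with all controls is a sensitivity analysis.*

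In the Discussion, list which of these criteria the historical cohorts did not record, and state that they remain a source of residual confounding.

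The cost is an eligibility pass over data from the research group's own cohorts, fewer controls and some precision. With both cohorts, power at 34% against 26% falls from about 90% to 86–88% if 20–30% of controls are removed. With the 401-patient cohort alone it falls from about 75% to 66–70%. Criteria absent from the records can only be approximated by diagnosis and department, so the filter reduces the mismatch without removing it.

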## Abstract

**Introduction:**

Hospital admission in older adults with multiple chronic conditions is associated with unwanted outcomes like readmission, institutionalisation, functional decline and mortality. Providing acute care in the community and integrating effective components of care models might lead to a reduction in negative outcomes. Recently, the first geriatrician-led Acute Geriatric Community Hospital (AGCH) was introduced in the Netherlands. Care at the AGCH is focused on the treatment of acute diseases, comprehensive geriatric assessment, setting patient-led goals, early rehabilitation and streamlined transitions of care.

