## Introduction

### Background

Throughout the western world, there is an increase in older adults requiring acute care. Inpatient services are mostly consumed by those over the age of 65.^1 2^ The Netherlands, like many other countries, recently (2015) implemented stay-at-home policies leading to an increase in frail older persons living longer in the community.^3^ These reforms juxtaposed with an increased ageing population contribute to increased acute care utilisation.^4^ There has been a 19% increase in emergency department (ED) visits by Dutch older adults based on data from 2015 versus 2017.^5 6^

Many older adults come to the hospital with complex and atypical health problems.^5 7^ When older persons are subsequently hospitalised, health outcomes are known to be poor,^8^ particularly in patients with geriatric syndromes such as cognitive impairment or mobility impairment.^9 10^ For example, previous research showed that 30% of older persons gained new disabilities and 20% were readmitted within 30 days postdischarge.^11 12^ Hospitalisation itself may contribute to these poor outcomes, as hospitalised older adults often have reduced mobility because they are bedbound for approximately 20 hours a day.^13 14^ Low physical activity, in combination with poor nourishment and increased caloric demand due to acute illness, can lead to the loss of muscle mass and may contribute to the development of new disabilities, particularly in frail patients.^15 16^ Together with the noise in a hospital environment and the different personnel rotating between patient rooms, this contributes to sensory overstimulation and sleep deprivation, which may lead to confusion and the occurrence of delirium.^17–19^ Not only is the patient affected during hospitalisation but the informal caregivers also find hospital admissions stressful.^20^ Furthermore, previous research shows that a lack of discharge planning in the hospital can result in patients’ care needs being unmet.^21^ Hospital care as usual compared with discharge planning and follow-up show a higher rate of early readmissions.^22^ Readmissions can further affect patients’ recovery and increase healthcare costs.^23^

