The AGCH delivers acute care that is focused on early mobilisation and rehabilitation. Older persons with common medical problems (such as urinary tract infections, pneumonia or heart failure) and geriatric syndromes requiring hospital admission can be admitted to the AGCH. The AGCH provides a form of *intermediate* care between primary and secondary care. In the Netherlands, primary care includes general practice, community nursing and (temporary) admission to a nursing home. Secondary care includes specialist medical care and hospital admission. The care at the AGCH is supervised by a geriatrician and provided by nurses trained in geriatric care who have experience as either a hospital or community nurse. The single rooms are designed to accommodate respite for the informal caregivers. This concept of care is new to the Netherlands, and to our knowledge, there is only one comparable example in Europe: a ‘subacute care unit’ in intermediate care, which has been implemented in Spain.^27^

Our hypothesis is that with the provision of integrated medical and nursing care close to home, the AGCH is better suited to the needs of older adults with multiple chronic conditions and will lead to better patient health outcomes and reduced post-acute care costs. Therefore, this study is designed to compare care provided for older patients in the AGCH versus care provided in a hospital setting. Specifically, we aim to:

Evaluate the 90-day readmission rate of patients acutely admitted to the AGCH compared with a traditional hospital (usual care). Secondary outcomes include functional decline, institutionalisation, healthcare utilisation, the occurrence of geriatric syndromes such as delirium, health-related quality of life (HRQOL), mortality and patient satisfaction;Assess the cost-effectiveness of the AGCH versus usual care by performing an economic evaluation from a healthcare provider and societal perspective;Conduct a process evaluation using interviews with key stakeholders to identify facilitators and barriers to the implementation of the AGCH.

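### The Transitional Care Bridge controls are not limited to usual-care patients, so some may have received a programme that overlaps with the AGCH intervention

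*Protocol article*

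**What the plan says.** - **Comparator.** The first aim (Introduction, Background) is to evaluate 90-day readmission at the AGCH "compared with a traditional hospital (usual care").
- **First control group** (Historical control groups): "The first control group from the Transitional Care Bridge Study consists of 674 patients who were recruited between September 2010 and March 2014". The same paragraph adds: "They participated in a negative randomised controlled trial that assessed the effectiveness of a nurse-led transitional care programme in preventing functional decline". It gives no arm, allocation ratio, arm sizes or readmission result for that trial.
- **Second control group.** The observational Hospital-ADL study "consists of 401 patients who were recruited between October 2015 and June 2017". Both sources are introduced together: "We selected two completed cohort studies that were conducted by our research group as historical control groups". That label does not fit a randomised trial in which a programme was assigned.
- **Intervention.** The Abstract counts "early rehabilitation and streamlined transitions of care" among the elements of AGCH care.
- **The protocol's own premise on readmission** (Background): "Hospital care as usual compared with discharge planning and follow-up show a higher rate of early readmissions".
- **Adjustment** (Planned statistical analyses). Propensity weights are built from covariates that differ at baseline or are associated with 90-day readmission. Trial arm is not mentioned. The Discussion names non-randomisation, baseline differences and calendar time as limitations, but not programme exposure among controls.

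**The concern.** The definition of the first control group does not match the stated comparator. Followed as written, it would count patients randomised to the nurse-led programme as usual care. That programme addressed care transitions, which the AGCH also sets out to improve, so such controls would have received something close to one component of the intervention under test.

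Two things are at stake. The first is what is being estimated: with programme patients included, the control condition is a mixture of usual care and usual care plus a programme. The second is bias in the primary outcome if the programme changed readmission. The description of the trial as negative does not close the question. It refers to functional decline, whereas the primary outcome here is unplanned readmission at 3 months, and utilisation and cost are also compared.

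**Working it through.** **Inputs from the protocol.** AGCH rate 26%; control rate 34%, taken from Hospital-ADL; 515 evaluable AGCH patients; two-sided alpha 0.05; 80% power; cohorts of 674 and 401.

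**Inputs the protocol does not give (assumptions).** The share *s* of the 674 who received the programme (0.5 used here); the programme's relative risk *RR* for readmission (a range is shown); a usual-care rate of 34% in the first cohort too; pooling of the two cohorts, with the first cohort alone as an alternative.

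**Step 1: the plan's own figure.** With equal groups and pooled null variance,

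n = [1.960·√(2·0.30·0.70) + 0.842·√(0.34·0.66 + 0.26·0.74)]² / 0.08² = 514 per group.

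The protocol states 515, and 515 against 515 gives 80.1% power. The figure reproduces. It does not depend on the first cohort, because the 34% comes from Hospital-ADL.

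**Step 2: control rate with programme patients included.**

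p_c = 0.34 × [1 − w·s·(1 − RR)], where w is the first cohort's share of the controls.

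Pooled, w = 674/1,075 = 0.627. With s = 0.5, 337 patients were treated, and 337/1,075 = 31% of controls.

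- RR 0.9: 0.34 × (1 − 0.627·0.5·0.1) = 32.9%, a difference of 6.9 points from 26%.
- RR 0.8: 0.34 × (1 − 0.627·0.5·0.2) = 31.9%, a difference of 5.9 points.

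**Step 3: power with 515 AGCH patients and m controls, unweighted.**

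Power = Φ[(d − 1.960·SE₀)/SE₁], where d = p_c − 0.26, SE₀ uses the pooled proportion and SE₁ the separate ones. For m = 1,075 and RR 1, SE₀ = 0.0249 and SE₁ = 0.0241, so (0.08 − 0.0488)/0.0241 = 1.29 and power is 90%.

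| Controls (m) | RR | Control rate | Difference (points) | Power |
|---|---|---|---|---|
| Both cohorts (1,075) | 1.00 | 34.0% | 8.0 | 90% |
| | 0.95 | 33.5% | 7.5 | 86% |
| | 0.90 | 32.9% | 6.9 | 81% |
| | 0.80 | 31.9% | 5.9 | 67% |
| | 1.10 | 35.1% | 9.1 | 96% |
| First cohort alone (674) | 1.00 | 34.0% | 8.0 | 85% |
| | 0.90 | 32.3% | 6.3 | 66% |
| | 0.80 | 30.6% | 4.6 | 41% |
| Usual care only, both cohorts (337 + 401 = 738) | n/a | 34.0% | 8.0 | 86% |
| Usual care only, first cohort (337) | n/a | 34.0% | 8.0 | 71% |

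The RR 1.10 row matters: if the programme raised readmission, the AGCH effect is overstated, and the higher power belongs to a wrong estimate.

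**Step 4: can the planned adjustment remove it?** No. Programme assignment is a treatment given after baseline, not a baseline characteristic. Recruitment to that trial ended in March 2014 and the AGCH opened in July 2018, so no index AGCH stay could have been in the programme arm. There is therefore no overlap on arm to balance, and weights built on baseline covariates leave the exposure in place.

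**The case against.** The protocol discloses the trial origin openly. The 674 were all conventionally hospitalised patients, the study design section speaks of hospital controls, and calling the trial negative reads as the reason for treating the cohort as usual care. Readers are sent to the cited papers for detail, and a condensed article may leave the choice of arm to a fuller document. If a bias toward no effect did arise, it would be conservative. At RR 0.9 the pooled power is still 81%.

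Much of this stands against stronger readings that a reader might infer:

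- *The whole trial was taken and many controls were treated.* This is a natural reading, but the text does not say whether 674 is the full trial or a subset, and it gives no allocation.
- *The comparison is biased toward no effect.* This needs the programme to have lowered readmission. The Background sentence makes that plausible, but it is a general statement about early readmission and not a result of this programme at 3 months.
- *Functional outcomes are contaminated in the same way.* The only evidence in the document is that the trial was negative on functional decline, which argues against this.

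What does not stand is the idea that nothing needs to change. The article itself fixes the control group's source, size and dates, and that definition does not match its comparator. The referral to other papers covers the methods and inclusion criteria of those studies, not which arm is used here. Nor is the error conservative in every case: an adverse programme effect would reverse it. Extra programme contacts, if counted, could also raise control utilisation and cost even if the programme had no clinical effect.

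**Conclusion.** The concern holds in conditional form. The protocol uses participants of a randomised transitional-care trial as usual-care controls without limiting them to the usual-care arm. If programme patients are among the 674, the comparison is not purely AGCH against usual care. If the programme also changed readmission, the AGCH estimate is biased toward no effect (programme beneficial) or away from it (programme harmful); with no programme effect on readmission, this bias is zero.

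The documents do not allow the bias to be computed. The illustration of 8 points shrinking to 6.9 or 5.9, and power falling from 90% to 81% or 67%, rests on assumed half allocation, pooling, a 34% rate in both cohorts and relative risks of 0.9 or 0.8. It also ignores the loss of precision from propensity weighting. The 401 Hospital-ADL controls and the target of 515 are unaffected.

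This should be settled before the analysis, but it falls short of a defect that must be fixed before the study can stand. Confidence is moderate.

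**What to change.** 1. State in the control-group section which arm or arms the 674 comprise, with the number in each, and describe the source as a randomised trial.
2. Restrict this control group to patients randomised to usual care in the main primary, secondary and economic comparisons.
3. Report the full group as a sensitivity analysis by trial arm.
4. If the 674 are already usual-care patients only, one sentence saying so resolves the point.

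**Cost.** No new data should be needed, since the research group ran the trial and should hold the allocation. The price is fewer controls. Under the half-allocation assumption, pooled power goes from 90% to 86% if the programme had no effect on readmission. It is equal at 86% if the programme's relative risk was 0.95, and restriction gains power at the lower relative risks shown. If the first cohort is compared on its own, the loss is larger: from 85% to 71% when the programme had no effect.
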